### Preoperative medication

All patients will be routinely administered levofloxacin or tobramycin eye drops (four times a day for 3 days) before surgery to minimise the risk of infection. An intramuscular injection of ethamsylate (1 mg/kg)^14^ will be used 30 min before surgery to reduce bleeding.

### Anaesthesia

General anaesthesia or retrobulbar anaesthesia will be used according to the standard clinical routine.

### Surgery methods management

The choice of surgical methods depends on the degree of ectopia lentis and the state of zonules. If the extent of the unhealthy zonules (broken or weak) is ≤180°, phacoemulsification and in-the-bag IOL implantation (with or without capsular tension ring) will be used. Otherwise, the capsular bag will be removed, and IOL will be fixed through trans-scleral fixation. Surgery will be performed by the same surgeon (DZ). Rayner 920H/970C or Sensar AR40e will be used as the implanted IOL.

The surgical techniques for patients who received in-the-bag IOL implantation are as follows: a 3.0 mm corneal tunnel incision will be made at 12 o’clock. Then, a continuous circular capsulorhexis will be performed manually. Iris hooks will stabilise the bag, and the lens will be aspirated with a phacoemulsifer. IOL will be implanted in the bag, and the capsular tension ring will be implanted when the IOL cannot be stably fixed.

For patients who received trans-scleral fixation of IOL, the surgical techniques will be performed as the previous study described.^8^ In brief, a 3.0 mm corneal tunnel incision will be made at 12 o’clock. Then, a continuous circular capsulorhexis will be performed manually, and the capsular bag will be removed after the phacoaspiration. Trans-scleral fixation of IOL will be performed with the two IOL haptics sutured by 8-0 polypropylene at 2.0 mm posterior to the corneal limbus. Anterior vitrectomy will be performed when severe vitreous prolapse occurs.

### Postoperative management

After surgery, tobramycin and dexamethasone eye drops (four times a day) and ointment (once every night) will be routinely administered for 1 week. If intraocular pressure (IOP) is higher than 25 mm Hg, topical IOP-lowering medication will be used. If IOP is higher than 40 mm Hg, an intravenous drip of 20% mannitol will be used.^15^ In case necessary, anterior chamber drainage will be performed through the side incision.

### Outcome measures

#### Primary outcome

The primary outcome is the change of BCVA and the incidence of complications (time frame: non-surgical group is evaluated at the first visit and 1, 2, 3 years after enrolment; surgical group is evaluated at preoperation, 3 months, and 1, 2, 3 years postoperatively).

#### Secondary outcomes

Change of axial length (time frame: non-surgical group is evaluated at the first visit and 1, 2, 3 years after enrolment; surgical group is evaluated at preoperation, 3 months, and 1, 2, 3 years postoperatively).High-order aberrations (time frame: non-surgical group is evaluated at the first visit and 1, 2, 3 years after enrolment; surgical group is evaluated at preoperation, 3 months, and 1, 2, 3 years postoperatively).Central cornea endothelial cell loss (time frame: preoperation, 3 months, and 1, 2, 3 years postoperatively).The state of zonules (time frame: non-surgical group is assessed at the first visit and 1, 2, 3 years after enrolment; surgical group will be assessed preoperatively).Anterior chamber angle (time frame: non-surgical group is assessed at the first visit and 1, 2, 3 years after enrolment; surgical group will be assessed preoperatively, 3 months, and 1, 2, 3 years postoperatively).Tilt and eccentricity of IOL (time frame: 3 months, and 1, 2, 3 years postoperatively).IOP (time frame: non-surgical group is evaluated at the first visit and 1, 2, 3 years after enrolment; surgical group is evaluated at preoperation, 3 months, and 1, 2, 3 years postoperatively).Aortic root diameter (time frame: non-surgical group is evaluated at the first visit and 1, 2, 3 years after enrolment; surgical group is evaluated at preoperation and 1, 2, 3 years postoperatively).Aortic root (sinuses of Valsalva) Z-score, adjusted by body surface area (Z-score) (time frame: non-surgical group is evaluated at the first visit and 1, 2, 3 years after enrolment; surgical group is evaluated at preoperation and 1, 2, 3 years postoperatively).Incidence of valvular heart disease (time frame: non-surgical group is evaluated at the first visit and 1, 2, 3 years after enrolment; surgical group is evaluated at preoperation and 1, 2, 3 years postoperatively).Body mass index (BMI) (time frame: non-surgical group is evaluated at the first visit and 1, 2, 3 years after enrolment; surgical group is evaluated at preoperation and 1, 2, 3 years postoperatively).Metacarpophalangeal joint length (time frame: non-surgical group is evaluated at the first visit and 1, 2, 3 years after enrolment; surgical group is evaluated at preoperation and 1, 2, 3 years postoperatively).Choroidal thickness (time frame: non-surgical group is evaluated at the first visit and 3 years after enrolment; surgical group is evaluated at preoperation and 3 years postoperatively).Choriocapillaris flow deficits (time frame: non-surgical group is evaluated at the first visit and 3 years after enrolment; surgical group is evaluated at preoperation and 3 years postoperatively).Genetic mutation state of patients (time frame: preoperation).Vision-related quality of life (time frame: non-surgical group is evaluated at the first visit and 3 years after enrolment; surgical group is evaluated at preoperation and 3 years postoperatively).

### Examinations

Baseline data and follow-up examination items are as follows:

Demographic characteristics, including name, gender and date of birth.Slit-lamp examination: slit-lamp examination (BQ-900, Haag Streit, Switzerland) and fundus examination will be performed at each visit.Visual acuity and refraction: the uncorrected visual acuity and BCVA will be evaluated with Early Treatment of Diabetic Retinopathy Study (ETDRS) LogMAR visual acuity chart (Precision Vision, Villa Park, Illinois, USA) at a test distance of 4.0 m. The refractive error will be determined by subjective refraction following an objective measurement. Spherical equivalent will be obtained with the calculation of spherical power plus half of the cylindrical power.Axial length measures: axial length will be measured using IOLMaster 700 (Carl Zeiss, Jena, Germany).High-order aberrations will be assessed using Nidek OPD-Scan III (Gamagori, Japan).Corneal endothelial cell counting and morphology will be detected using an endokeratoscope (SP-2000P, Topcon, Japan).The state of zonules will be assessed clock by clock with ultrasound biomicroscopy. The clock range of zonular disruption or loosening will be recorded. These results will be confirmed using slit-lamp photography after dilation.The structure of the anterior chamber angle will be examined using a Tomey Casia 2 anterior segment optical coherence tomography (OCT) (Tomey, Tokyo, Japan).^16^
The tilt and eccentricity of IOL will be evaluated using Pentacam AXL (Oculus, Germany).^17^
IOP measures: the IOP in the patient’s eyes will be measured using a non-contact tonometer at each visit, and the average of the three measures will be taken.Echocardiography examination: this examination will be performed using Doppler echocardiography (HP/Philips Sonos 5500, Philips, Bothell, Washington, USA). A skilled technician will measure the aortic root diameter. Z-score will be calculated using the Marfan foundation’s calculator (https://marfan.org/dx/zscore-children/). Normal Z-score ranges from −2 to 2. A dilated aortic root is defined as a Z-score ≥2.0. A larger Z-score is associated with an increased risk of aortic complications such as dissection, rupture and valvular regurgitation. An experienced cardiologist will determine the presence or absence of heart valve disease.BMI: BMI is a person’s weight in kilograms divided by the square of height in metres. The normal range for the Chinese population is 18.5–23.9. A higher BMI can indicate higher levels of body fat.Metacarpophalangeal joint length will be measured in hand radiograph.The choroidal thickness and choriocapillaris flow deficits will be measured using posterior segment OCT and OCT angiography (Zeiss Cirrus 5000 with AngioPlex).Gene detection: genomic DNA from each subject in the study will be analysed by whole-exome sequencing to detect mutations and diagnosis.Vision-related quality of life will be assessed using the Pediatric Eye Questionnaire.^18^
Adverse events or complications will be collected at each visit.

### Workflow

The workflow will be carried out in the order mentioned above, starting with patients’ recruitment and ending with a minimum of 3 years’ follow-up (figure 1). The non-surgical group will be followed up 1, 2 and 3 years after enrolment. The surgical group will be followed up at 3 months, and 1, 2, 3 years postoperatively. The examinations planned for each follow-up time point are shown in online supplemental table 1.

10.1136/bmjopen-2023-072542.supp1Supplementary data

**Figure 1 F1:**
[figure not shown]
Flow chart of the study. *The surgery will be performed when either of the following situations occurs. BCVA, best-corrected visual acuity; CEL, congenital ectopia lentis.

### Data collection and management

The case report form (CRF) will collect basic demographic and clinical information. Results of eye examinations will be recorded on paper, and questionnaires will be filled out in the paper form. Original data will enter the lens dislocation case database at the Zhongshan Ophthalmic Center. After the study, relevant documents will be stored securely at the Zhongshan Ophthalmic Center for 10 years for specific scientific research purposes.

### Statistical analysis plan

Statistical analysis will be performed using Stata V.15.0 (StataCorp, College Station, Texas, USA). Quantitative data conforming to a normal distribution will be described as the mean±SD. The difference between the baseline and follow-up data will be compared by one-way analysis of variance. The median±IQR will describe the quantitative data of the skewness distribution. The Wilcoxon signed-rank test will be used to compare these data’s differences. For qualitative data described as proportions, the Χ^2^ test or Fisher’s exact test will be used to compare the differences between groups. P<0.05 is considered statistically significant. The differences and 95% CI in the changes of BCVA and other parameters will be calculated. The univariable linear regression model will estimate these changes and their associated factors. All variables with p<0.05 in the univariable regression analysis will be included in the multivariable linear regression model.

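### One-way ANOVA, an independent-groups test, is named for comparing baseline and follow-up values of the same patients; followed as written it loses power

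*Protocol article*

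**What the plan says.** The Primary outcome section of the protocol article states: "The primary outcome is the change of BCVA and the incidence of complications". The time frame is repeated in the same people: the "non-surgical group is evaluated at the first visit and 1, 2, 3 years after enrolment" (four time points), and the "surgical group is evaluated at preoperation, 3 months, and 1, 2, 3 years postoperatively" (five time points).

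The Statistical analysis plan section then sets the test by distribution:

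- Normal data: "The difference between the baseline and follow-up data will be compared by one-way analysis of variance". No repeated-measures form and no patient term is named.
- Skewed data: "The Wilcoxon signed-rank test will be used to compare these data’s differences".

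Two further sentences bear on change. One is "The differences and 95% CI in the changes of BCVA and other parameters will be calculated"; the other is "The univariable linear regression model will estimate these changes and their associated factors". Neither is tied to the ANOVA. The significance threshold is 0.05.

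**The concern.** One-way ANOVA compares independent groups. Here the groups would be visits, and each patient appears in all of them. The test leaves the stable differences between patients in its error term, although those differences cancel when each patient is compared with himself or herself.

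The section also disagrees with itself. The signed-rank test is paired and the one-way ANOVA is not, yet both serve the same before-and-after question. Which one is used depends on whether the data look normal, which has nothing to do with whether they are paired.

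The sentence covers the BCVA half of the primary outcome when BCVA is judged normal, and on the same condition axial length, intraocular pressure and aortic root diameter. The study is meant to inform the timing and method of surgery. A non-significant result from an underpowered test could be read there as evidence of stability.

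**Working it through.** **Inputs from the document.** Four or five visits per patient (Primary outcome section); one-way ANOVA for normal data and a 0.05 threshold (Statistical analysis plan section). The plan gives no power or precision figure for BCVA change. Its one calculated size is for complication incidence: 1.96² × 0.15 × 0.85 / 0.03² = 544.2, and 544/0.9 = 604.4. This agrees with the stated 544 and 604 and does not depend on the ANOVA.

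**Inputs assumed.** The within-patient correlation ρ between visits is not given; I take 0.3, 0.5 and 0.7. The SD σ is taken as equal at each visit.

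**Two visits, n patients.**

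- SE of the mean change, paired: σ√(2(1−ρ)/n).
- SE if the visits are treated as independent groups: σ√(2/n).
- Ratio: 1/√(1−ρ).
- True size of a nominal 5% test: 2 × [1 − Φ(1.96/√(1−ρ))].
- Power against an effect that a paired test detects with 80% power (1.96 + 0.84 = 2.80 paired SEs): 1 − Φ(1.96/√(1−ρ) − 2.80).

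| ρ | SE ratio | Critical value in paired SEs | True size | Power (paired = 80%) |
|---|---|---|---|---|
| 0.3 | 1.20 | 2.34 | 1.9% | 68% |
| 0.5 | 1.41 | 2.77 | 0.6% | 51% |
| 0.7 | 1.83 | 3.58 | 0.03% | 22% |

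An interval built with the unpaired SE would cover 98.1%, 99.4% and 99.97% instead of 95%. At ρ = 0 the two analyses agree.

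**More than two visits.** With no true change and equal correlations, the between-visit mean square has expectation σ²(1−ρ), while the one-way error mean square is close to σ². The F ratio therefore centres near 1−ρ instead of 1.

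A simulation shows the effect for four visits. It used 4,000 runs, equal correlations, an assumed 272 patients (half of 544, not a documented group size) and an assumed step of 0.15 SD at every follow-up visit.

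| ρ | Size, one-way | Size, repeated measures | Power, one-way | Power, repeated measures |
|---|---|---|---|---|
| 0.3 | 1.3% | 5.2% | 33% | 56% |
| 0.5 | 0.2% | 5.2% | 27% | 72% |
| 0.7 | 0 of 4,000 runs | 5.4% | 17% | 92% |

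With five visits the one-way size is about 0.7%, 0.05% and 0 of 4,000 runs. The power figures depend on the shape of change: for a linear drift ending at 0.15 SD over four visits and ρ = 0.5, they are 15% against 57%. The direction is the same throughout.

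**The case against.** **Repeated-measures ANOVA may have been meant.** This is possible, since an article condenses its protocol. But the text names a specific unpaired test next to a specific paired one, so a reader who follows it will run the wrong analysis. The wording needs correcting either way.

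**The ANOVA is one of several analyses.** This stands. The section ranks no test as the main one, and the ANOVA applies only if BCVA is judged normal. The plan also provides estimates of change with intervals and a regression on change. The complications half of the primary outcome, which sets the sample size, is untouched.

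**The error is on the cautious side.** This also stands. With positive correlation a significant result from this test can still be trusted; a non-significant one cannot be read as stability.

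Two stronger readings are tempting:

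- *That the confidence intervals for BCVA change are wrong.* The sentence on intervals is separate from the ANOVA sentence. Intervals computed from each patient's own change would be valid.
- *That two eyes per patient are counted as independent, which would raise false positives, or that missed visits are mishandled.* The article mentions the patient's eyes only for measuring intraocular pressure. It states neither a unit of analysis nor a missing-data rule, and a condensed article may leave both to the full protocol or analysis plan. No error can be inferred from that silence.

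**Conclusion.** The point holds in a limited form. For normally distributed outcomes the article names an independent-groups test for paired data, at odds with the paired test it names for skewed data. The consequence is p-values that are too large and lost power, without extra false positives.

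The loss is moderate at ρ = 0.3 and severe by 0.7. These sizes are illustrative: the correlation, equal SDs, 272 patients, 0.15 SD effect and shape of change are all assumptions. A weaker link between preoperative and postoperative BCVA would shrink the loss in the surgical group. The confidence intervals are at risk only if they come from the ANOVA or from visits pooled without a patient term.

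**What to change.** In the Statistical analysis plan section, replace the one-way ANOVA by a paired or repeated-measures analysis within each group. A suitable choice is a linear mixed model with:

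- visit as a fixed effect;
- baseline as one of the response visits, and therefore not also a covariate;
- a random patient effect, plus eye within patient if both eyes are analysed.

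Take the 3-year change in BCVA and its 95% confidence interval from that model, and say so, which also settles where the intervals come from. A paired t-test for a two-visit contrast, or a repeated-measures ANOVA, would also cure the defect.

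The cost is a change of wording and slightly more analysis work. No new data or visits are needed, and the study is scheduled to run to December 2027.

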**Trial registration number:**

NCT05654025.

STRENGTHS AND LIMITATIONS OF THIS STUDYThis study is a cohort of congenital ectopia lentis (CEL) in the Chinese population with a relatively large sample size and a comparatively long (5 years) follow-up.This study assesses important ophthalmic measurements with significant clinical implications, including visual acuity, intraocular pressure, axial length, high-order aberrations, choroidal thickness and choriocapillaris flow deficits.Important systemic indicators of Marfan syndrome are measured, including the metacarpophalangeal joint length, incidence of valvular heart disease, aortic root diameter and Z-score.In this study, CEL in age less than 3 years old is excluded and participants could be lost to follow-up after surgery.This study focuses on individuals with CEL, but different subtypes of CEL may not be classified.

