### Sample size

Sample size will be estimated as follows: assuming the incidence of complications in patients with CEL is 15%, and the margin of error is 20%. For a 5% significance level, Z_α/2_ is 1.96 for the two-tailed alternative hypothesis. Sample size=(Z_α/2_)^2^×P(1−P)×1/E^2^=(1.96)^2^×15%×(1–15%)/(15%×20%)=544. Assuming the loss ratio of 10%, the adjusted sample size will be 544/(1–0.1)=544/0.9=604.

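### The planned crude-proportion test for 3-year complication incidence does not use partial follow-up, so the estimate and group comparison can be biased if loss is related to complications or differs by group

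*Protocol article*

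**What the plan says.** All references are to the protocol article.

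- **Primary outcome:** "The primary outcome is the change of BCVA and the incidence of complications". The time frames are that the "non-surgical group is evaluated at the first visit and 1, 2, 3 years after enrolment" and the "surgical group is evaluated at preoperation, 3 months, and 1, 2, 3 years postoperatively".
- **Statistical analysis plan:** "For qualitative data described as proportions", the chi-square "test or Fisher’s exact test will be used to compare the differences between groups". The section does not name complications. Its other methods (analysis of variance, Wilcoxon signed-rank, linear regression) are for quantitative data, so this sentence is the one that covers complication incidence. It names no method that allows for censoring.
- **Sample size:** "Assuming the loss ratio of 10%, the adjusted sample size will be" 604, up from 544. This is the only numerical response to loss.
- **Strengths and limitations list:** "participants could be lost to follow-up after surgery". No rate is given, overall or by group.
- **Examinations and Study monitoring:** complications are collected at every visit, and each withdrawal or loss is to be recorded and explained in the case report form.

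**The concern.** A proportion compared by chi-square or Fisher's exact test needs one binary value per patient at a common horizon. A patient seen at 1 year and then lost has no 3-year value. The analyst must leave that patient out, keep the patient in the denominator with whatever was seen, or mix the two. These choices give different answers, and none uses the time at risk.

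Inflating the sample keeps the number of completers near 544 and so keeps the planned interval width. It does nothing if those who leave differ in risk from those who stay. At stake are the incidence for which the study was sized (15% within 3 percentage points) and the surgical versus non-surgical comparison, which unequal loss can distort. The point concerns patients lost to follow-up, not those who move from observation to surgery.

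**Working it through.** **Inputs from the Sample size section:** incidence 15%; relative margin 20%, so E = 0.15 × 0.20 = 0.03; Z = 1.96; loss 10%.

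**Assumed here (not in the article):** constant hazards, the risk of lost patients relative to those who stay, and loss rates by group.

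**1. The plan's own figure.** n = Z²P(1−P)/E² = 1.96² × 0.15 × 0.85 / 0.03² = 544.2, stated as 544. Then 544/0.9 = 604.4, stated as 604. Both are reproduced. (The denominator as printed lacks the square. Only the squared value gives 544, so this is a separate slip with no effect on the number.)

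**2. 10% loss independent of risk, true 3-year risk 15%.** Event hazard λ = −ln(0.85)/3 = 0.0542 per year; loss hazard μ = −ln(0.90)/3 = 0.0351 per year. The probability that an event is seen before loss is λ/(λ+μ) × (1 − 0.85 × 0.90) = 0.607 × 0.235 = 0.143. The probability of being event-free with full follow-up is 0.85 × 0.90 = 0.765.

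| Handling of lost patients | Expected proportion |
|---|---|
| All lost patients left out (completers only) | 15.0% |
| Events before loss counted, event-free afterwards, all enrolled in denominator | 14.3% |
| Only event-free losses left out: 0.143/(0.143 + 0.765) | 15.7% |
| All lost patients counted complication-free: 0.90 × 0.15 | 13.5% |
| Kaplan-Meier, censored at loss | 15.0% |

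The 14.3% assumes events are seen up to the moment of loss. If they are seen only up to the last visit attended, the value lies between 13.5% and 14.3%.

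**3. 10% loss related to risk, 15% in those who stay.**

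- Lost patients left out: bias = 0.10 × (0.15 − risk in the lost). This is +0.75 points if their risk is half, −1.5 if double and −3.0 if triple.
- All lost patients counted complication-free: bias = −0.10 × risk in the lost. This is −1.5 points at equal risk, −3.0 if double and −4.5 if triple.

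**4. The same in whole patients.** 604 enrolled, 60 lost, 544 × 0.15 ≈ 82 events in completers, observed 82/544 = 15.07%.

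- No lost patient has an event: 82/604 = 13.6% (13.5% in step 2; the gap is rounding to 82).
- Risk tripled in the lost: (82 + 60 × 0.45)/604 = 109/604 = 18.05%, which is 2.97 points above 15.07%.
- All lost patients have an event: (82 + 60)/604 = 23.5%.

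**5. Unequal loss, same true risk of 15% in both groups.** With 5% and 15% lost and all counted complication-free: 0.95 × 0.15 = 14.25% and 0.85 × 0.15 = 12.75%, a spurious difference of 1.5 points. With 5% and 30% lost uniformly over 3 years and events before loss counted, a lost patient has a chance of 1 − 0.15/0.1625 = 7.7% of an event being seen (0.1625 = −ln 0.85). The proportions are 0.95 × 0.15 + 0.05 × 0.077 = 14.6% and 0.70 × 0.15 + 0.30 × 0.077 = 12.8%, a difference of 1.8 points.

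**The case against.** A reader might infer that the plan drops lost patients or counts them as complication-free. It says neither. The Statistical analysis plan section has one general sentence on qualitative data, and a condensed article may leave the denominator and the missing-data rule to a fuller document. That absence is not charged here. Other handling also fits the text: proportions by visit among those seen would keep early complications in the early figures.

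A reader might also infer that the primary incidence is biased. That does not follow. A completers-only proportion is unbiased if loss is unrelated to risk, and nothing in the article shows that it is related. The limitations list says only that loss after surgery could happen. It does not say that the groups will lose patients at different rates. The 30% in step 5 is three times the planned loss.

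Nor does ordinary loss push the estimate past its 3-point margin. Under independent loss the shift is about 0.7 points if events before loss are counted. Leaving lost patients out reaches the margin only when their risk is about tripled. Finally, Kaplan-Meier also assumes independent loss, so it does not cure the 18.0% and 23.5% cases.

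All of this stands and limits the size of the point. It does not defend the stated test. By-visit proportions still give no 3-year figure that uses partial follow-up, and the visit data needed for a better estimate will be on file.

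**Conclusion.** The point holds as a matter of analysis choice. For a 3-year incidence with expected loss, the article names a crude-proportion test that does not use partial follow-up, and its only numerical response to loss is a larger sample. The estimate can be biased if loss is related to complications, and the comparison can be distorted if loss differs by group.

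At the planned 10% loss, independent of risk, the shift runs from none (completers only) through about 0.7 points (14.3%) to 1.5 points (13.5%), against a planned half-width of 3.0. It reaches 3.0 points only if the lost have about three times the risk and are left out, or twice the risk and are all counted complication-free. The 13.6% to 23.5% range is a bound, not an expectation.

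These sizes rest on the plan's 15% and 10%, and on the constant hazards, relative risks and group loss rates assumed above. The point covers one of the two primary components; change in BCVA is not analysed by this test.

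**What to change.** In the Statistical analysis plan section, replace the chi-square or Fisher's exact test for complication incidence with the following:

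- Estimate the 3-year cumulative incidence of complications by group, from enrolment or from surgery as in the stated time frames. Use a method that allows censoring at the last visit: Kaplan-Meier or Aalen-Johansen, interval-censored where only the visit of detection is known.
- Compare groups by the difference in 3-year cumulative incidence with its 95% CI.
- Because this still assumes loss independent of risk, report loss by group with the recorded reasons, and a best-case/worst-case range for the lost patients.

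If a fuller analysis plan already does this, only the article's wording needs to be aligned. The 544 and 604 do not change, and no new data are needed, since complications are collected at each visit and losses are already recorded. The cost is a little more analysis work and a slightly wider interval.

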## Introduction

Congenital ectopia lentis (CEL) is a rare ocular disease characterised by the dislocation or displacement of the lens. Several systemic diseases have been reported to be associated with CEL, such as Marfan syndrome, homocystinuria, Weill-Marchesani syndrome and Ehlers-Danlos syndrome.^1^ However, some patients with CEL may have no known systemic manifestations.^2^

Patients with mild lens dislocations can be treated with conservative methods (eg, corrective eyeglasses or contact lenses).^3^ However, progressive subluxation or complete dislocation of the lens can cause a high degree of myopia or astigmatism, even amblyopia.^4^ Surgical intervention is crucial in the management of patients with severe CEL.^5^ Currently, there is no unified standard for operation timing for CEL. A previous study recommended surgical intervention when the near vision of children was worse than 0.4 in LogMAR acuity.^6^ However, some researchers suggested that surgery should be performed when the best-corrected visual acuity (BCVA) is less than 0.3 or monocular diplopia occurs.^4 7^ Few studies have focused on the refractive change and visual prognosis in patients with CEL both with conservative management and surgical management.^8^

Several surgical techniques have been reported over the past decades, such as lensectomy, phacoemulsification without intraocular lens (IOL) implantation, phacoemulsification and IOL implantation (with or without capsular tension ring) and various trans-scleral fixations of IOL.^9–11^ However, the safety and efficacy of these techniques have not been fully validated so far, especially in the Chinese population. Herein, we will conduct this cohort study at the Zhongshan Ophthalmic Center, one of the biggest ophthalmic hospitals in China.^12^ All children diagnosed with CEL will be followed up for at least 3 years. Long-term changes in BCVA and the incidence of complications will be evaluated in patients with conservative and surgical management.

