### Eligibility criteria

#### Inclusion criteria

Diagnosed with congenital lens dislocation and age ≥3 years old.Agree to participate in this study with written informed consent from patients or legal guardians.

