#### Exclusion criteria

History of ophthalmic trauma or other ophthalmic surgeries.Combined with other ophthalmic diseases such as primary glaucoma, uveitis and corneal disease.Patients who could not cooperate in the examinations.

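### Relatives may enrol in this cohort with a genetically investigated disease, but the named analyses treat all patients as independent; if relatives enrol, some intervals and tests will be miscalibrated.

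*Protocol article*

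**What the plan says.** All places are in the protocol article.

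- **Who may enter.** Apart from consent, the only inclusion criterion is "Diagnosed with congenital lens dislocation and age ≥3 years old". The exclusions begin with "History of ophthalmic trauma or other ophthalmic surgeries" and go on to other eye disease and inability to cooperate. Neither list mentions relatives, and there is no upper age limit.
- **The disease.** The Introduction states: "Several systemic diseases have been reported to be associated with CEL, such as Marfan syndrome, homocystinuria, Weill-Marchesani syndrome and Ehlers-Danlos syndrome". It adds that some patients may have no known systemic signs.
- **Genetics.** Under Examinations, "genomic DNA from each subject in the study will be analysed by whole-exome sequencing to detect mutations and diagnosis". Mutation state is also a secondary outcome.
- **Analysis.** The Statistical analysis plan section names one-way analysis of variance, the Wilcoxon signed-rank test, chi-square or Fisher's exact tests, and 95% confidence intervals for changes. On regression it says: "The univariable linear regression model will estimate these changes and their associated factors". Variables with p<0.05 then enter a multivariable linear model. No term or variance adjustment for related patients is named.
- **Sample size.** 544 patients, or 604 after 10% loss, based on the precision of a single 15% complication incidence. No design effect is applied.

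**The concern.** The protocol itself treats the disease as one with a genetic cause worth sequencing in everyone. Siblings, or a parent and child, who both have ectopia lentis meet the entry criteria. Relatives can share a mutation and, through it, similar eyes, similar systemic traits and similar complication risk. The methods named count each patient as a separate, independent piece of information. This dependence is between patients, so analysing one eye per patient would not remove it.

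The primary results are at stake first: an incidence or mean change would carry an interval that is too narrow. Next are any factors that relatives share. For these, the independent unit is closer to the family than to the patient, and the p<0.05 screen would let them into the multivariable model more often than its nominal level implies.

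**Working it through.** **Step 1. The plan's own figure.** The inputs from the Sample size section are P = 15%, a relative margin of 20% (so E = 0.15 × 0.20 = 0.03), z = 1.96 and 10% loss.

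- n = 1.96² × 0.15 × 0.85 / 0.03² = 544.2
- 544 / 0.9 = 604.4

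Both stated figures reproduce. The printed denominator lacks its square (taken literally it gives 0.4898 / 0.03 = 16.3), but the result uses the squared value. With 544 independent patients the half-width is 1.96 × √(0.15 × 0.85 / 544) = 3.0 percentage points.

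**Step 2. Design effect.** Let a share f of patients be in families of size m, the rest be single cases, and ρ be the within-family correlation of the outcome. For a mean or incidence:

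- DE = 1 + f(m − 1)ρ
- effective n = 544 / DE
- half-width = 3.0 × √DE
- real level of a nominal 5% test of a fully family-shared factor ≈ 2[1 − Φ(1.96 / √DE)]

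The document gives none of f, m or ρ. All three are assumptions.

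| f | m | ρ | DE | True SE / naive SE | Effective n | Half-width (points) | Real level |
|---|---|---|---|---|---|---|---|
| 0 | – | – | 1.00 | 1.000 | 544 | 3.00 | 5.0% |
| 10% | 2 | 0.1 | 1.01 | 1.005 | 539 | 3.01 | 5.1% |
| 10% | 3 | 0.5 | 1.10 | 1.049 | 495 | 3.15 | 6.2% |
| 30% | 2 | 0.3 | 1.09 | 1.044 | 499 | 3.13 | 6.0% |
| 50% | 2 | 0.5 | 1.25 | 1.118 | 435 | 3.35 | 8.0% |
| 50% | 3 | 0.5 | 1.50 | 1.225 | 363 | 3.67 | 11.0% |

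**Step 3. Which regression factors are affected.** Ordinary linear regression was simulated under the null with N = 544, a binary factor of 30% prevalence, f = 10–50%, m = 2–3, ρ = 0.3–0.5 and 4,000 runs per scenario. Rejection rates at nominal 5% were:

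- factor shared by the whole family: 5.6%–10.6%
- factor independent within families: 4.4%–5.6%, which is nominal within simulation error

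**Step 4. Families split between the groups.** If a share f of patients is in pairs with one member in each of two equal groups, the variance of the difference is multiplied by 1 − fρ, so the ordinary test is conservative. With ρ = 0.5:

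- f = 20%: factor 0.90, real level 2[1 − Φ(1.96 / √0.90)] = 3.9%
- f = 40%: factor 0.80, real level 2[1 − Φ(1.96 / √0.80)] = 2.8%

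So the direction of the error depends on the comparison.

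**The case against.** The strongest reply is that nothing in the article says relatives will be sought, screened or enrolled. Recruitment runs through outpatient clinics with no family-based step. Much of the text also points to a mainly paediatric cohort: the Introduction speaks of children, and the instruments are a paediatric eye questionnaire and a children's Z-score calculator. Parent–child pairs may therefore be uncommon. With few relatives the effect is negligible: at 10% of patients in families of two or three and a correlation up to 0.5, standard errors grow by at most 5%. The regressions also model changes, in which stable traits shared as levels partly cancel, so a high correlation is not assured. Finally, a condensed article can leave a variance option to the full analysis plan.

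Most of this stands, and it is why the point is conditional and minor. It does not remove the point. Siblings qualify even in a purely paediatric cohort, and the section commits to specific methods that do not fit related patients if they enter. Family membership is easy to record at enrolment and harder to reconstruct later.

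A reader might infer more than the document supports:

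- **That the disease is largely one of inherited syndromes.** The Introduction reports associations and says that some patients may have no systemic signs.
- **That relatives tend to be milder and so drift into the non-surgical group.** No text supports this. If it were so, it would split families between the groups and make that comparison conservative.
- **That every association in the regressions is overstated.** Step 3 shows no inflation for factors that vary independently within families.
- **That a genotype regression is planned.** Mutation state is listed as an outcome. Its use as a regressor is only a possible reading of the unspecified list of factors.

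**Conclusion.** The point holds in conditional form, as a low-cost improvement. Entry is open to relatives, every subject is sequenced, and the named tests, intervals and regressions assume independent patients. If relatives enrol and their outcomes are positively correlated:

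- intervals for incidences and mean changes are too narrow
- tests of family-shared factors reject too often
- comparisons that split families between groups may be conservative
- factors that vary independently within families are essentially unaffected

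Over the assumed range (10–50% of patients in families of two or three, correlation 0.1–0.5) the design effect is 1.01–1.50, and a nominal 5% test of a family-shared factor has a real level of 5.1%–11.0%. The lower end is trivial; the upper end needs half the cohort to be in trios. It would be wrong to state as fact that the plan's standard errors are too small, because the document does not give the quantities that decide this. On this point the sample size of 544 and 604 is not wrong on its own inputs.

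**What to change.** 1. Add a family identifier to the case report form at enrolment, shared by all related participants.
2. In the Statistical analysis plan section, state that regressions and the confidence intervals for changes and incidences use standard errors clustered by family, in Stata with vce(cluster family).
3. When relatives are present, replace the chi-square or Fisher comparison of proportions with a family-clustered binomial model or GEE. Clustering also corrects the error bars where families are split between the groups.
4. Add a sensitivity analysis with one patient per family, chosen by a rule fixed in advance, such as the first enrolled.

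The cost is one field on the form, one option in the Stata commands and one extra analysis. Some intervals will be slightly wider. If no relatives enrol, results are essentially unchanged.
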